## Abstract

**Background:**

Several strategies are recommended to alleviate clinical symptoms of ulcerative colitis (UC). Soy milk may affect UC through its anti-inflammatory properties. However, no study has examined the effects of soy milk consumption on gut microbiota and inflammatory biomarkers in patients with UC. The current study will be done to examine the effects of soy milk consumption on UC symptoms, inflammation, and gut microbiota in patients with UC.

**Methods:**

This study is a randomized clinical trial, in which thirty patients with mild to moderate severity of UC will be randomly allocated to receive either 250 mL/day soy milk plus routine treatments (*n* = 15) or only routine treatments (*n* = 15) for 4 weeks. Assessment of anthropometric measures and biochemical indicators including serum concentrations of high-sensitivity C-reactive protein (hs-CRP), tumor necrosis factor-α (TNF-α), interleukin-1β (IL-1β), and interferon gamma (IFN-γ) will be done at the study baseline and end of trial. In addition, the quantity of butyrate-producing bacteria including *Clostridium* cluster IV, *Faecalibacterium prausnitzii*, and *Roseburia* spp.; prebiotic bacteria including *Lactobacillus* spp. and *Bifidobacteria* spp.; and mucus-degrading bacteria including *Akkermansia muciniphila*, *Bacteroides fragilis*, and *Ruminococcus* spp., as well as calprotectin and lactoferrin levels, will be explored in fecal samples. Also, the *Firmicutes* to *Bacteroidetes* ratio which is of significant relevance in human gut microbiota composition will be assessed.

**Discussion:**

Altered gut microbiota has been reported as an important contributing factor to inflammation in patients with inflammatory bowel disease (IBD). Soy milk contains several components such as phytoestrogens with potential anti-inflammatory properties. This product might affect gut microbiota through its protein and fiber content. Therefore, soy milk might beneficially affect systemic inflammation, gut microbiota, and then clinical symptoms in patients with UC.

**Trial registration:**

Iranian Registry of Clinical Trials (www.irct.ir) IRCT20181205041859N1. Registered on 27 January 2019.

## Background

Inflammatory bowel disease (IBD) is a chronic gastrointestinal disease associated with high disability and a high cost for patients as well as for the health care system [1–4]. Epidemiological studies have shown that more than 10 million people suffer from IBD worldwide [4]. National estimates in Iran showed that 40 persons among 100,000 people are affected [5]. The most common type of IBD is ulcerative colitis (UC) that is characterized by inflammation and ulceration of the mucosal layer of the colon, and its patients usually suffer from rectal bleeding (with or without mucus), diarrhea, tenesmus, and abdominal pain when the disease relapsed [6, 7].

Several studies have been done to find an appropriate strategy to control the disease symptoms and inflammation in patients with UC [8]. Patients with UC might take benefit from the consumption of fish oils, polyunsaturated fatty acids, and probiotics [9–11]. Soy and its products have been shown to have anti-inflammatory properties, particularly in patients with diabetes mellitus and cardiovascular diseases [12–15]. Due to the inflammatory nature of UC, consumption of soy products may affect UC disease symptoms as well. However, to our knowledge, no study was done to assess the efficacy of soy consumption on inflammatory markers and clinical outcomes in UC patients. In an experimental study, consumption of soy milk, fermented with six lactic acid bacteria strains, prevented the shortening of colon length, breaking of epithelial cells, lowering liver and thymus weights, and enlargement of spleen in mice fed dextran sodium sulfate (DSS) used for inducing IBD [16]. In another study on DSS-treated mice, soy protein administration reduced weight loss, colon shortening, splenomegaly, and colonic inflammation [17].

A large number of studies have shown a link between gut microbiota and UC [18–20]. In a review article, Bellavia et al. concluded that imbalanced gut microbiota is involved in UC pathogenesis [18]. Moreover, abnormalities of intestinal microbiota in UC patients, compared with healthy individuals, were reported in a case-control study [19]. These abnormalities may induce gut inflammation and consequently systemic inflammation [20]. In addition, the link between gut microbiota abnormalities and UC symptoms has been shown in earlier studies [21–23]. Balancing the gut microbiota through fecal microbiota transplantation can relief UC symptoms [23]. There are several investigations that indicated favorable association of soy products with balanced gut microbiota; of them, a cross-sectional study revealed that lower intake of soy drinks was associated with a reduced abundance of potentially beneficial bacteria and increased potentially harmful bacteria in the colonic mucosa of healthy individuals [24]. In a randomized clinical trial, Fernandez-Raudales et al. reported that soy milk consumption resulted in a potentially beneficial alteration in the *Firmicutes* to *Bacteroidetes* ratio in the gut [25]. Soy protein administration, compared with cow milk protein intake, resulted in a beneficial change in gut microbiota in an experimental study as well [26].

Among all soy products, soy milk can be a good choice for UC patients because they are recommended to limit their consumption of milk [27], which might prohibit them meeting their calcium requirement. Although not a rich source of calcium, soy milk can provide at least part of calcium requirements in these patients [16]. Therefore, we designed this study to examine if soy milk consumption can influence gut microbiota, inflammatory markers, quality of life, symptoms, and disease severity in patients with UC.

## Material and methods

### Participants

This is a randomized clinical trial which will be done in Tehran, Iran, in 2018–2019. Outpatients with UC will be recruited from the gastrointestinal (GI) clinic of the Shariati Hospital, Tehran, Iran. UC will be confirmed by a gastroenterologist through the use of colonoscopy and laboratory findings [28].

### Inclusion criteria

We will include (1) patients with mild to moderate UC, (2) those who are between 20 and 60 years, (3) patients at the remission stage of disease with stable medication therapy, and (4) those with body mass index (BMI) of 18.5–30 kg/m^2^. To determine disease severity, the partial-Mayo scale will be applied. Based on this scale, scores of 3–8 are considered as mild to moderate UC [29].

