### Sample size calculation

Considering the type I error of 5% (*α* = 0.05) and type II error of 20% (*β* = 0.20, power = 80%) and fecal concentrations of calprotectin as the key variable, we manually, without the use of any software, calculated required sample size using the following formula [30]:
$$ n=\frac{2\left[{\left(a+b\right)}^2\times {\upsigma}^2\right]}{{\left({\mu}_1-{\mu}_2\right)}^2} $$

*n* = sample size in each group.

*μ*_1_ = mean for fecal calprotectin in the intervention group (we considered it as 424 μg/g based on the study of Morshedzadeh et al. [31]).

*μ*_2_ = mean for fecal calprotectin in the control group (which was considered as 602 μg/g based on the study of Morshedzadeh et al. [31]).

σ = variance (SD) for mean concentrations of calprotectin, which was considered as 141 (the average SDs reported for fecal calprotectin in the control and intervention groups of Morshedzadeh et al.’s study [31]).

*a* = conventional multiplier for alpha = 0.05 that was 1.96.

*b* = conventional multiplier for power = 0.80 that was 0.842.

Overall, based on the formula and given a 50% drop-out in each group, we will need a sample size of 15 persons for each group. Due to frequent visits (about 6 visits) that each participant would have throughout the study, we considered the drop-out rate as much as 50%. However, we would try our best to keep the drop-outs as low as possible.

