### IBD severity

The severity of IBD will be examined using the 9-point partial Mayo score designed by Sutherland et al. (the questionnaire is available in Supplementary file, section D) [29]. This scale composes of three categories including rectal bleeding (0 = none, 1 = visible blood with stool less than half the time, 2 = visible blood with stool half of the time or more, 3 = passing blood alone), stool frequency (0 = normal, 1 = 1–2 stools/day more than normal, 2 = 3–4 stools/day more than normal, 3 = > 4 stools/day more than normal), and physician assessment (0 = normal, 1 = mild, 2 = moderate, 3 = severe) that each gets 0–3 score. By summing up these scores, we will have a total score of 0–9. Greater scores show higher severity of disease.

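### The inclusion criteria require both remission and a partial Mayo score of 3–8, which conflict on the protocol's own scale, so the enrolled population depends on which criterion recruiters apply

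*Protocol article*

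**What the plan says.** The Inclusion criteria section of the protocol article lists four conditions joined by 'and'. The first concerns severity: "We will include (1) patients with mild to moderate UC". The third concerns disease stage: "patients at the remission stage of disease with stable medication therapy". The same section makes the first condition operational: "To determine disease severity, the partial-Mayo scale will be applied", and "scores of 3–8 are considered as mild to moderate UC".

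The IBD severity section defines the scale. Rectal bleeding, stool frequency and physician assessment are each scored 0 to 3. "By summing up these scores, we will have a total score of 0–9", and "Greater scores show higher severity of disease".

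The Background describes rectal bleeding, diarrhea, tenesmus and "abdominal pain when the disease relapsed" as what patients usually experience in relapse. The Abstract's Methods paragraph describes the participants only as having mild to moderate disease and does not mention remission. No section defines remission, and none says that the 3–8 band refers to past severity.

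**The concern.** Both criteria appear to describe the patient's state at entry, and both must be met. A partial Mayo score of 3 or more records current bleeding, raised stool frequency, a physician's judgement of active disease, or a mixture of these. Remission ordinarily means that these are absent or nearly so. If the two cannot both be satisfied, whoever screens patients has to give way on one of them, and the protocol does not say which.

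Two things are at stake. The first is to whom the result applies: patients with symptoms, patients in remission, or an unplanned mixture. Disease stage is not among the stratification and matching factors in Study design and intervention (age, gender, BMI, type of medicines), so a mixture would not be balanced by design. The second is whether a listed primary outcome can respond. Assessment of variables names IBD severity as primary, and how far that score can fall depends on where patients start.

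**Working it through.** **Inputs.** From IBD severity: three items, each scored 0, 1, 2 or 3; bleeding 0 means none, frequency 0 means normal, and physician assessment runs from 0 (normal) through 1 (mild) and 2 (moderate) to 3 (severe). From Inclusion criteria: the 3–8 band.

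**Step 1, the plan's own range.** The minimum is 0 + 0 + 0 = 0 and the maximum 3 + 3 + 3 = 9. This reproduces the stated range of 0–9.

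**Step 2, all profiles.** There are 4 × 4 × 4 = 64 item profiles.

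- Totals of 0, 1 and 2 arise in 1, 3 and 6 ways: 10 profiles at 2 or less.
- A total of 9 arises in 1 way.
- The 3–8 band therefore holds 64 − 10 − 1 = 53 profiles.

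**Step 3, profiles without bowel symptoms.** Fix bleeding = 0 and frequency = 0. Only the physician item varies:

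| Physician rating | Total | In the 3–8 band? |
|---|---|---|
| normal (0) | 0 | no |
| mild (1) | 1 | no |
| moderate (2) | 2 | no |
| severe (3) | 3 | yes |

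One profile of the 53 is free of both symptoms, and it requires the physician to call the disease severe. That patient is hard to describe as in remission, or as mild to moderate. The remaining 53 − 1 = 52 profiles all have visible blood, raised stool frequency, or both.

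**Step 4, near-remission profiles.** Allow no bleeding and a frequency score of at most 1. Three profiles then reach the band: (0, 0, 3), (0, 1, 2) and (0, 1, 3), in the order bleeding, frequency, physician. Each needs a physician rating of moderate or severe.

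**Step 5, comparison with the Background.** That section associates bleeding and diarrhea with relapse. The symptoms that put a patient in the 3–8 band are thus the ones the article itself links to relapse.

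**Step 6, room to improve.** The score cannot fall below 0. A patient starting at 0–2 can improve by at most 2 points. One starting at 3–8 can improve by 3 to 8 points, depending on the starting value.

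The counts are of possible profiles, not of patients. They show what the scoring rule allows, not how often each profile occurs in the clinic.

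**The case against.** The strongest objection is that remission is undefined. The Background sentence is descriptive: it says what patients usually suffer in relapse, not that patients outside relapse have no symptoms. The third criterion couples remission with stable medication, and the Non-inclusion criteria bar patients with a change of medicine or a hospital stay in the last 3 months. On a loose reading, remission could mean stable and not flaring. A patient scoring 1 + 1 + 1 = 3 could then meet both criteria.

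Part of this stands. A reader might infer that the criteria admit nobody. The article does not support that, because it depends on a meaning of remission that the article never gives. The loose reading, however, has no textual support either. Stable medication is stated as a condition in addition to remission, recent changes of medicine are dealt with separately, and the 1 + 1 + 1 patient has visible blood in the stool.

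It can also be said that the numeric band is the only operational entry rule, that the Abstract agrees with it, and that severity is measured at baseline in everyone, so the enrolled population would be visible in the data. That is fair, and there is no evidence that recruiters would act differently from patient to patient. But seeing afterwards who was enrolled does not settle beforehand who should be.

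Two further inferences are tempting. One is that the trial would be underpowered if patients in remission were enrolled. The article gives no calprotectin mean or SD for remission, and a lower mean need not reduce power if the SD falls in proportion, so no power figure can be attached. The other is that the planning values in Sample size calculation (424 µg/g for intervention; 602 µg/g as the "mean for fecal calprotectin in the control group") presuppose active disease. They are taken from a cited study whose disease stage the article does not state. Nor does the conflict show that severity should cease to be a primary outcome: a trial in remission can legitimately measure worsening.

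**Conclusion.** The concern holds as a contradiction in the entry rule. On any ordinary reading of remission, criteria (1) and (3) conflict: 52 of the 53 profiles in the 3–8 band carry bleeding or raised stool frequency, and the other needs a physician rating of severe. Nothing in the article reconciles them, and a fuller document could not make both rules work as written without giving remission an unusual meaning. The enrolled population therefore depends on which criterion is applied.

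The demonstrable consequence for the outcomes is the difference in room to improve on the severity score: at most 2 points from a start of 0–2, against 3 to 8 points from a start of 3–8. The conclusion assumes that both criteria refer to the patient's state at entry and that remission has roughly its usual sense. It does not establish that recruitment is impossible, and it implies no particular loss of power. It must be fixed, because eligibility decides who is randomized and no later analysis can change that.

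**What to change.** Before recruitment, the sponsor should:

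1. Reconcile criteria (1) and (3) in Inclusion criteria into a single population defined on the partial Mayo score, with stable medication kept as its own condition. If the word remission is retained, define it on the same score.
2. Make the Abstract's description of participants agree.
3. Confirm that the calprotectin values in Sample size calculation (424 and 602 µg/g, SD 141) come from patients at the chosen disease stage. If they do not, restate the planning figures.

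This review does not say which disease stage is right.

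The cost is a short amendment to the eligibility text with a matching change to the registry entry where needed. No procedure is added. The number of patients changes only if step 3 shows that the planning values do not fit the chosen population and the recalculation gives a different size.

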### Non-inclusion criteria

Patients will not be included if they (1) changed type or dosage of their medicines over the last 3 months; (2) were hospitalized in the last 3 months; (3) were diabetics or were affected by celiac or other gastrointestinal diseases including cancers and infectious diseases; (4) were pregnant or lactating; (5) consumed antibiotics, pre- or probiotic products, multi-vitamin, and mineral supplements during the last 3 months; and (6) were current smokers.

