### Exclusion criteria

We will exclude individuals who change the type or dosage of their medicines during the intervention, those that are not willing to continue intervention, and individuals who suffer from probable complications related to soy milk consumption. Figure 1 shows the study flowchart.

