### Study design and intervention

The diagram for Standard Protocol Items: Recommendations for Interventional Trials (SPIRIT) is shown in Fig. 2. After recruiting participants, participants will be stratified based on age (20 to 40 and 40 to 60 years), gender (male/female), BMI (18.5 to 24.9 and 25 to 30), and type of medicines (anti-inflammatory and immunosuppressant) into different blocks and will be randomly allocated to the intervention or control groups. For each patient in a certain block, a matched person in terms of abovementioned variables would be placed in that block. Then, these two patients in a given block would be randomly assigned to the intervention and control groups. To do randomization, an identification code will be given to each eligible patient, and then, code of patients with the same age, gender, BMI, and medication will be stated in the lottery container, and finally, patients with the same conditions will be randomly assigned to the intervention or control groups. Random allocation will be done by a person who is unaware about the aim of our study. Patients in the intervention group (*n* = 15) will receive 250 mL/day preservative-free soy milk along with routine treatments that they were taking for their condition. Participants in the control group (*n* = 15) will receive only routine treatments. The intervention will last for 4 weeks. The assessment of primary and secondary outcome variables will be done at the study baseline and end of trial. Participants in both groups will also receive usual dietary recommendations for IBD patients based on European Society for Parenteral and Enteral Nutrition (ESPEN) guideline [32]. This guideline will be explained to patients by an experienced nutritionist. Given that preservative-free soy milk will be expired within 12 days after production, three 1-L bottles of soy milk will be delivered to patients in intervention group every 12 days (at the study baseline, day 12, and day 24). At the study baseline and day 12, patients in the intervention group will received 3 1-L bottles of soy milk (used during 12 days), and at day 24, they will received 2 1-L bottles of soy milk (used during 8 days). Due to the unfavorable taste of soy milk, patients in intervention group will be asked to consume it at night before sleep. They should consume a 250-mL glass of soy milk every night. Participants will be instructed in a class, prior to the start of trial, about the quantity of soy milk they have to consume in a day. A standard glass (which contained 250 mL soy milk) will be shown to participants, and all will be asked to use the same glass to make sure that the daily portion they are consuming is the one the investigators requested. To control this, participants will be contacted every day and they will be asked to send us the photo of the glass they are using for soy milk drinking. At each delivery of soy milk bottles, patients will be monitored for soy milk consumption and will be asked to give back the empty bottles. Participants’ compliance will be assessed using the following formula: (number of used packages/all given packages) × 100. In addition to assessment of compliance, consumption of soy milk will be monitored by phone call every week. In addition, collecting three 1-day dietary recalls from participants throughout the study can further help computing the compliance to soy milk intake. Participants will be asked not to change their lifestyle, dietary habits, and medicines during the study.

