## Discussion

Currently, some medications including amino salicylates, glucocorticosteroids, immune modulators, antibiotics, and anti-TNF drugs are prescribed for IBD patients, which cause severe adverse effects such as increasing anti-antibody reactions, risk of allergy, infection, and mutagenesis [54–56]. Thus, finding a food with therapeutic effects and without toxicity is of great importance for IBD patients. Soy products such as soy milk with anti-inflammatory properties are a good choice for inflammatory diseases including diabetes mellitus and cardiovascular diseases [12, 13, 57]. However, so far, no study has examined the effects of soy milk consumption on inflammatory markers and disease symptoms in patients with IBD. In addition, the beneficial effects of soy milk consumption on gut microbiota have been reported [58]; however, these effects have not been yet assessed in IBD patients. As recently stated, change in the gut microbiota has been a contributing factor to IBD incidence, particularly UC [59–61]. In addition, it has been shown that gut microbiota imbalance can affect disease symptoms [62].

In this study, we hypothesize that soy milk consumption might have a beneficial effect in IBD patients through increasing abundance of beneficial/commensal bacteria and reduction of mucus-degrading taxa. Soy milk contains 0.6 g/100 g fiber which can be considered as a prebiotic [63]. It has long been shown that prebiotics can favorably affect gut microbiota [64]. In an experimental study, soy milk administration resulted in an increase in *Firmicutes* to *Bacteroidetes* ratio in gut microbiota community of rats [58]. Also, soy milk intake had an increasing effect on *Lactobacillus* spp. which potentially protects against gut inflammation [65]. In addition to fiber, protein content of soy milk can affect gut microbial community [66, 67]. In an experimental study on golden Syrian hamsters, soy protein, compared with milk protein, could alter diversity of gut microbial community [68].

Patients with IBD cannot easily tolerate lactose-containing foods such as dairy products [68, 69]. Soy milk as a lactose-free milk might be a good alternative for dairy products in IBD patients. Overall, finding dietary strategies to improve disease severity and symptoms in IBD patients is of high importance. This approach could be much more cost-effective than prescription of medications for long-term use in these patients.

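### The eligibility and diet rules do not say how existing soy use is handled, so a habitual soy-milk user may enrol and, as a control, be told to continue

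*Protocol article*

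**What the plan says.** All references are to the protocol article.

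- **Non-inclusion criteria**, item 5, rules out patients who "consumed antibiotics, pre- or probiotic products, multi-vitamin, and mineral supplements during the last 3 months". Neither the four inclusion criteria nor the six non-inclusion criteria mention soy intake, soy allergy or soy intolerance.
- **Exclusion criteria**: soy appears only here, where the protocol removes "individuals who suffer from probable complications related to soy milk consumption". This acts after a patient has received the product.
- **Study design and intervention**: one arm receives 250 mL of soy milk daily for 4 weeks on top of routine treatment, and the other receives routine treatment alone. No placebo drink is described. For diet, "Participants will be asked not to change their lifestyle, dietary habits, and medicines during the study". The sentence is not limited to one arm, and no sentence asks controls to avoid soy.
- **Discussion**: "Soy milk contains 0.6 g/100 g fiber which can be considered as a prebiotic".
- **Background**: in a cross-sectional study of healthy people that the authors cite, "lower intake of soy drinks was associated with a reduced abundance of potentially beneficial bacteria".
- Three 1-day dietary recalls are planned, at weeks 2, 3 and 4. No baseline recall is described.

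**The concern.** The 3-month criterion keeps out patients recently exposed to products that act on the gut microbiota, which is among the primary outcomes. By the protocol's own account soy milk may be such a product, yet the criterion does not name it. The request for unchanged habits then preserves whatever soy use a patient brings in. A control who already drinks soy milk would go on doing so, and a soy-arm patient with the same habit would start from an exposed baseline. Both reduce the difference that the trial is built to detect. In a trial of 15 per arm, a null result would be harder to interpret, because no soy effect and too little separation in soy intake would look alike.

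A second, smaller gap concerns soy-related complications. They are handled only once they have occurred, and the eligibility text does not say how an already known allergy or intolerance is dealt with before allocation.

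**Working it through.** **Step 1. Follow one patient through the rules.** Take a patient who drinks soy milk daily and meets every other criterion.

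- *Eligible?* This depends on whether soy milk counts as a prebiotic product under item 5. The Discussion supports a yes. The criterion is silent, and screening staff could decide either way.
- *If enrolled as a control:* the diet instruction tells the patient to continue.
- *If enrolled in the soy arm:* the baseline sample is taken under existing soy use.
- *Does anything later restore the contrast?* Randomisation strata are age, gender, BMI and type of medicine, not soy. The covariance analysis adjusts for the baseline outcome and for confounders that differ between groups. If habitual users are evenly spread, soy use does not differ between groups and nothing is adjusted, but the contrast is still reduced. The recalls could reveal soy intake in controls, but they begin after baseline and no such use is stated.

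**Step 2. Reproduce the planned sample size.** Inputs from Sample size calculation: means 424 and 602 μg/g (difference 178), SD 141, "conventional multiplier for alpha = 0.05 that was 1.96" and "conventional multiplier for power = 0.80 that was 0.842".

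n = 2 × (1.96 + 0.842)² × 141² / 178² = 9.85, so 10 per group before drop-out. The stated 15 is 10 × 1.5. Whether that is the right allowance for 50% drop-out is a separate matter.

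**Step 3. Illustrate attenuation.** Assume that a share p of patients in each arm already has the full soy effect and gains nothing from more. The difference becomes 178 × (1 − p). The protocol gives no value for p. The SD is held at 141.

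With 10 evaluable per arm, the standard error is 141 × √(2/10) = 63.06, and normal-approximation power is Φ(difference / 63.06 − 1.96).

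| Assumed p | Difference (μg/g) | Difference / 63.06 − 1.96 | Power, 10 per arm | Power, 15 per arm | Evaluable n per arm for 80% power |
|---|---|---|---|---|---|
| 0% | 178.0 | 0.86 | 81% | 93% | 10 |
| 5% | 169.1 | 0.72 | 77% | 91% | 11 |
| 10% | 160.2 | 0.58 | 72% | 88% | 13 |
| 20% | 142.4 | 0.30 | 62% | 79% | 16 |
| 30% | 124.6 | 0.02 | 51% | 68% | 21 |

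The 15-per-arm column uses a standard error of 141 × √(2/15) = 51.49 and assumes that nobody drops out.

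With 10 per arm, p = 10% is one habitual user per arm and p = 20% is two.

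**The case against.** **The trial may be asking an add-on question.** Soy milk plus routine care against routine care, on an unchanged diet, is a legitimate comparison, and randomisation spreads habitual soy use over both arms. This stands as far as bias goes. A reader might infer that background soy use invalidates the comparison or could create a spurious benefit. The documents do not support that: the effect is attenuation. The add-on reading does not explain, however, why other prebiotic exposure is ruled out and soy is not.

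**Item 5 may already cover soy milk.** Taken with the Discussion, it can be read that way, so the flat statement that a daily soy-milk drinker is eligible would go too far. What stands is the ambiguity.

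**The unchanged-habits sentence is protective.** It discourages controls from taking up soy and limits other dietary drift. This stands, and the sentence should be kept.

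**Habitual users may be few.** The protocol calls the taste of soy milk unfavorable. Against this, it says that these patients are advised to limit milk and presents soy milk as a good alternative. Neither remark gives a number. A reader might infer that the contrast is in fact diluted; the text supports this only if such patients enrol.

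**The power figures are hypothetical.** They rest on an invented share and complete saturation. The 178 μg/g is also not shown to be a soy effect, since the authors say that no soy study on inflammatory markers exists in these patients. This stands, and the figures are illustration only.

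**Allergy may be covered elsewhere.** A reader might infer that allergic patients will be exposed. The consent form is not shown and may address allergy, and patients know what they would be drinking. The documents show only that the eligibility text is silent and that the one soy-related rule acts after exposure.

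**Conclusion.** The point holds as an ambiguity with a possible cost in sensitivity. The non-inclusion criteria and the Discussion leave open whether soy counts as a prebiotic product. If it does not, the diet instruction keeps existing soy use going in controls. Neither the baseline adjustment nor the planned recalls, as described, restores the lost contrast.

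The direction is towards no difference. The size cannot be estimated from the document, which gives no prevalence of soy use. Under the stated assumptions (10 evaluable per arm, SD 141, full saturation, 10% or 20% of the contrast lost), power would be about 72% or 62% against 81%; with all 15 per arm evaluable it would be about 88% or 79% against 93%. These figures show that one or two such patients per arm could matter in a trial this small. They are not a forecast.

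On allergy and intolerance, the conclusion is limited to a gap between the eligibility text and the exclusion rule. The change is worth making because it is cheap, not because harm or dilution has been shown.

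**What to change.** 1. **Non-inclusion criteria, item 5:** reconcile with the Discussion by stating that regular use of soy milk or soy products falls under the existing 3-month criterion.
2. **Study design and intervention:** keep the request for unchanged lifestyle, diet and medicines. Add that, as the one exception, both arms avoid soy products other than the study product for the 4 weeks.
3. **Dietary recalls:** tabulate soy intake by arm from the three recalls already planned, so that a reader can see how far the arms were separated.
4. **Eligibility and Exclusion criteria:** reconcile the two on how known soy allergy or intolerance is handled before randomisation. The rule itself is for the investigators to set.

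The cost is a screening question on soy use, one line of participant instruction, one table from data already being collected, and a short clarification of the eligibility text. The downside is that a few habitual soy users become ineligible.
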